### Recruitment

#### Home location catchment areas

The recruitment groups (< 1-mile, between 1 and 2 miles, and > 2 miles) were selected to ensure variability in distance to LRT from participants’ home location. We consider the 2 + mile group to be unexposed, as research shows few people in the US travel further than 2 miles by bike to reach transit [75–77]. We identified walk catchment areas within the described network distances from any Metropolitan Transit System (MTS) trolley station (i.e., the Blue line or any connecting trolley line). Since pedestrians travel along transportation networks, we used network-based catchment areas which have a much more accurate representation of urban form features accessible within a given walk distance. A “sausage” or balloon network buffer was developed to define all areas within the catchment areas with a 25-m (82 feet) trim or setback from the roadway. This expanded polygon intersects with parcels and land uses that front on the selected road segments so that homes and apartment buildings could be spatially matched to the buffers. Each catchment area was intersected with census block groups to determine the percentage of block groups contained. Block groups with less than 25% of their area in the buffer were not included. Figure 2 shows the LRT stations and recruitment catchment areas.

**Fig. 2 Fig2:**
[figure not shown]
LRT stations with recruitment catchment areas MTS LRT stations (red), census block groups within one mile with at least 25% area overlap with station areas (green), block groups between one and two miles (white), block groups greater than 2 miles (no-LRT-group) with at least 25% area overlap with two-mile catchment areas (beige). Figure created by authors

The primary recruitment strategy is to identify interested and eligible staff through a pre-screening survey invitation sent by UCSD’s Department of Resource, Management and Planning, in both English and Spanish. The email was sent to > 17,000 active UCSD career staff, identified by their job title code. This method allows us to target staff specifically, exclusive of students and faculty. The email contains an embedded link to the study screener from our secure study database. Those who choose to complete the pre-screening survey provide their contact information, home address or nearest intersection, and answer the eligibility screening questions. The home addresses of staff who meet the initial screening criteria are then geocoded and spatially joined to the recruitment catchment buffers to determine which catchment area they live in. Those who are not eligible receive an email and a phone call explaining the reasons for ineligibility. Those who meet eligibility criteria are contacted by research staff who confirm interest and eligibility, answer questions, and obtain written informed consent.

In addition to university email, we are recruiting through UCSD staff distribution listservs and flyers, staff associations and unions, and on-campus advertising. These recruitment efforts target key UCSD units like Housing, Dining and Hospitality services, the Black, Chicanx/Latinx, and Pan-Asian Staff Associations, and hospital nursing and support staff groups to reach the intended population. Recruitment began in January 2022 and is ongoing, with 230 participants currently enrolled.

### Survey testing sample

A sample of 40 UCSD staff was recruited to test the reliability of the study survey. After pre-testing near-final drafts, we evaluated the test–retest reliability and internal consistency of new survey items by administering it twice, roughly 2 weeks apart in a sample of 40 transit users and non-users in both Spanish and English. Participants met the same eligibility criteria as the full study sample.

### Sample size

The TROLLEY study will enroll 465 English or Spanish speaking staff from UCSD’s La Jolla campus. We estimated a sample size of 340 was needed, considering a baseline of 45.1 (SD: 4.6) minutes/week of moderate PA using NHANES (2005–06) adult accelerometer data. We used a meta-analysis by Hirsh et al. and a conservative expected change of 3.46 min/day (95%CI: 2.20, 4.72) in transit-related PA from Miller et al. that evaluated a similar intervention in Utah [62, 78]. We set a significance level of 0.05 and power levels of 95% and assumed a 20% attrition rate. However, to ensure sufficient power for planned moderator analyses and in case of higher attrition rates than planned, we will recruit a total sample of 465 participants, stratified by LRT exposure, income, and race/ethnicity.

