## Background

Reducing health inequalities and harms from physical inactivity and air pollution are UN priorities [1, 2]. Public transit provides an opportunity to address these major challenges by increasing physical activity (PA) through active transportation (AT), mitigating greenhouse gas (GHG) emissions by decreasing vehicle miles traveled (VMT), and providing equitable access to jobs, education, and healthcare. Safe and accessible transit is critical for low-income groups. Essential workers comprise 26% of the working age population and 40% of transit riders in the U.S. [3], and nearly 50% are people of color [4, 5]. Given that more than 80% of the U.S. population lives in urban areas, LRT has potential to impact a majority of the population and to deliver numerous co-benefits [6, 7].

Sufficient PA is associated with reduced risk of numerous chronic conditions, including cardiovascular disease (CVD), type 2 diabetes, cancer, stroke, hypertension, and premature mortality [8–11]. Regular PA is additionally linked with improved well-being, fewer depressive symptoms [12], less stress [13–15], and improved quality of life (QoL) [16–19]. Despite known health benefits, fewer than half of U.S. adults meet the recommendation of 150 min/wk of PA [10, 11, 20, 21]. Additionally, there are PA disparities by income and race/ethnicity [22–28]. While the prevalence of sufficient leisure time PA is stable or increasing in white and college-educated populations, minority, less-educated and low-income groups are experiencing declines and have lower PA levels overall [29, 30]. Transit use often involves walking or biking to stations or destinations and is associated with more minutes of PA and meeting PA guidelines [31–38], providing an approach to combat physical inactivity [39–41]. Furthermore, promoting active transportation helps reduce greenhouse gas and traffic-related air pollution emissions which offers substantial co-benefits [42].

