### Statistical approach

Summary statistics of individual-level demographics, census block attributes, and baseline values of all outcomes will be calculated for the full sample and compared between the LRT exposure groups. Variables that are not balanced across groups will be adjusted for in subsequent analyses. Daily minutes of MVPA are typically positively skewed and will be transformed as needed to better approximate normality. Longitudinal changes in outcomes across the 3 measurement time points will be assessed using multilevel mixed effects linear (for continuous outcomes) or multinomial or ordinal logistic (for categorical outcomes) regression models, with the measurement time point included as an independent variable and adjustment for individual or block group level covariates (i.e., demographic characteristics, walkability, etc.). Covariates will be selected using a priori-knowledge and Directed Acyclic Graphs. Each outcome will be modeled separately. As we will have multiple measurement days nested within participants, a random participant-level intercept will be included in all models (alternative approaches that consider such clustering based on generalized estimation equations (GEE) will be also tested as a sensitivity analysis). We will also test the extent of block group clustering for each outcome (without covariates) by including a random effect for the intercept at the block group level and estimating the intra-class correlation (ICC). A likelihood-ratio test will assess fit between the models with and without clustering and, if significant, a random effect for block group will be included. We will assess effect modification by LRT exposure and other variables on both additive and multiplicative scales (when focusing on binary, categorical or count outcomes) using traditional approaches (stratified analyses coupled with heterogeneity tests or by including an interaction term in our models) [112, 113].

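### The figure of 340 participants for 95% power does not follow from the inputs printed with it, so neither that power nor the moderator-power reason for enrolling 465 is supported

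*Protocol article*

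**What the plan says.** The Sample size section of the protocol article gives a complete set of planning figures:

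- result, baseline and spread: "We estimated a sample size of 340 was needed, considering a baseline of 45.1 (SD: 4.6) minutes/week of moderate PA"
- effect: "a conservative expected change of 3.46 min/day (95%CI: 2.20, 4.72) in transit-related PA"
- error rates and loss: "We set a significance level of 0.05 and power levels of 95% and assumed a 20% attrition rate"

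It then raises the target from 340 to 465, "to ensure sufficient power for planned moderator analyses and in case of higher attrition rates than planned". No moderator effect size or moderator power is given. The section does not name the test or contrast, the sidedness, the within-person correlation, or whether 340 already includes attrition.

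Three other places bear on these figures. Device measured outcomes defines the primary activity outcomes in minutes per day. Study sample and eligibility plans equal thirds by distance to light rail (LRT). Study Aims frames the travel hypotheses as those living closest to LRT against those with less access.

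**The concern.** Baseline and SD are per week, while the effect and the primary outcome are per day. The quantities differ too: moderate activity for the baseline, transit-related activity for the effect, and total activity and MVPA for the outcome.

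The SD is also only a tenth of the mean. That sits badly with two statements elsewhere. The Background says "fewer than half of U.S. adults meet the recommendation of 150 min/wk of PA", and the Statistical approach says "Daily minutes of MVPA are typically positively skewed".

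Two claims depend on this calculation: the 95% power, and the adequacy of 465 for the moderator analyses that carry the equity hypotheses. The Discussion leans on the second again when it credits the large sample with allowing effect modification to be determined. A reader who trusts these claims would give a null result more weight than the calculation can justify.

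**Working it through.** **Inputs (Sample size section unless noted).** Mean 45.1 and SD 4.6 min/week; effect 3.46 min/day; alpha 0.05 (taken as two-sided); power 95%; attrition 20%; stated result 340; target 465. Equal thirds come from Study sample and eligibility.

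**Formula.** Normal approximation, n per group = 2 × (1.960 + 1.645)² × (SD/effect)², where (1.960 + 1.645)² = 12.99. The total is then divided by 0.8 for attrition.

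**1. Reproducing 340 in one unit.** The effect is 3.46 × 7 = 24.22 min/week, which is 24.22/45.1 = 54% of baseline and 24.22/4.6 = 5.27 SDs. Then n per group = 2 × 12.99/5.27² = 0.94. Two groups need 1.9/0.8 = 2.3 in total and three groups 2.8/0.8 = 3.5, so about 2 to 4 people.

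**2. Ignoring the units.** 3.46/4.6 = 0.752 SD, so n per group = 2 × 12.99/0.752² = 45.9. Two groups need 91.9/0.8 = 115 and three groups 137.8/0.8 = 172.

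**3. Other routes.** One- and two-sided tests, one to three groups, unequal allocation, paired and difference-in-change designs with correlations from 0 to 0.7, and powers of 80% and 90% were also tried. With the stated effect and power, the nearest result is a three-group pairwise difference in change with zero within-person correlation: 276/0.8 = 345. Using the lower confidence limit of 2.20 for three groups gives 342 before attrition. Both treat min/day and min/week as the same unit.

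**4. Plausibility of the SD.** 45.1 ± 2 × 4.6 runs from 35.9 to 54.3, so if roughly normal about 95% of adults would lie between 36 and 54 min/week. The guideline of 150 min/week would lie (150 − 45.1)/4.6 = 22.8 SDs above the mean.

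**5. The SD that 340 would need.** Take 340 × 0.8 = 272 completers and an effect of 24.22 min/week.

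| Contrast | Calculation | SD needed (min/week) |
|---|---|---|
| Pairwise, three groups of 90.7 | 24.22 × √(90.7/25.99) | 45 |
| Two groups of 136 | 24.22 × √(136/25.99) | 55 |
| One-sample change, 272 | 24.22 × √(272/12.99) | 111 (SD of change) |

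These are about 10 to 24 times 4.6.

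**6. Moderators.** 465 × 0.8 = 372 completers, or 124 per distance group. Take a balanced binary moderator whose interaction equals the main effect. The standard error of the interaction is twice that of the main contrast, and power = Φ(z − 1.960).

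- *Printed inputs, one unit (weekly), 124 per group:* z is above 20, so power is about 100%.
- *Printed inputs, units ignored:* with two groups of 186, z = 3.63 and power is 95%; with 124 per group, z = 2.96 and power is 84%. A half-size interaction gives 44% and 32%.
- *Illustration only, supposing that 272 completers do give 95% power:* z = 3.605 × √(372/272)/2 = 2.11 and power is 56%. For a half-size interaction it is 18%.

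The answer runs from 18% to about 100% according to the reading chosen.

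**7. Attrition.** 1 − 272/465 = 0.415, so 272 completers would remain even after about 41% loss.

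**The case against.** A journal article may leave the test, the contrast and the correlation to the full protocol. That is right, and no weight is placed on their absence. The article does print mean, SD, effect, alpha, power, attrition and result together, and those figures disagree with one another.

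The results of 345 and 342 come close to 340. They emerge from a search over many variants, add assumptions that the article does not state, and still mix the two units, so they do not rescue the figure.

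A reader might infer that 4.6 is a standard error or a misplaced decimal. The documents do not show this: the article labels it an SD, and its source is not at hand. The Background's share meeting the guideline is only an upper bound, with no measurement method given, and the skewness remark concerns daily minutes. Implausible as a person-level SD is as far as the evidence goes.

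A reader might also infer that a simple before-after change was sized. The Sample size section names no contrast, so this cannot be asserted.

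Finally, a reader might infer that the plan's own figures show the moderator analyses to be underpowered. They do not. With units ignored, the printed inputs give 84% to 95% for an interaction as large as the main effect. The 56% and 18% borrow the disputed 340, and both interaction sizes are assumptions of this review.

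**Conclusion.** The point holds as an internal inconsistency. The printed inputs give about 2 to 4 participants in common units, or about 115 to 172 with units ignored, against a stated 340. The SD would have to be roughly 10 to 24 times larger to yield 340. The 95% power is therefore unsupported. The moderator-power reason for 465 is unsupported as well, because nothing valid lies beneath it. The reserve against attrition remains a sound reason for 465.

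These results rest on the normal approximation, a two-sided test, equal groups, and 340 including attrition. If 340 means people analysed, the SD needed rises to about 51 to 124 min/week and the conclusion is unchanged.

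This does not show that the study is too small. The documents give no SD of change. For near against far with 124 per group and a true difference of 3.46 min/day, power would be about 93% if that SD were 8 min/day and about 27% if it were 20. Both SDs are assumptions, and the documents do not allow a choice between them.

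**What to change.** Keep the target of 465 and rewrite the Sample size section as follows:

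1. Work in one unit, MVPA minutes per day, to match the primary outcome.
2. Use a person-level SD from whatever valid first-wave accelerometer files exist, or a stated range if there are too few. The Recruitment section reports 230 enrolled, not 230 usable files, and the Discussion notes many rescheduled measurement appointments.
3. State a range for the wave-to-wave correlation.
4. Name the contrast: change over time by distance to LRT.
5. Report power or minimum detectable difference at 372 completers, 124 per group.
6. Replace the moderator-power claim with a computed figure for a stated interaction size, or withdraw it. Keep the attrition reason.

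The cost is a small amount of analysis and a text correction. No extra participants are needed and the conduct of the study does not change. The drawback is that the restated power may be less favourable than 95%.

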### Data collection

Participants will complete a measurement visit after consenting to participation. Participants will be assessed 3 times during the 2 years they are enrolled in the study; once when first enrolled (2022), 1 year after enrollment (2023), and 2 years after enrollment (2024). All data collection will occur after the opening of the UCSD Blue Line Trolley. However, time 1 survey measures ask participants about commute, PA, and spending behaviors both at the time of assessment and, retrospectively, prior to the pandemic and the new LRT. The campus closure in March of 2020 due to COVID-19 provides a noteworthy reference point to aid recall. The UCSD Exercise and Physical Activity Resource Center (EPARC) distributes accelerometer and GPS devices and instructs participants how to wear the monitors. TROLLEY staff call participants during the wear week to ensure compliance. Links to the online surveys are emailed to participants, and participants receive a $50 gift card after completion of all assessments at each time point.

Study data are collected and managed using REDCap electronic data capture tools hosted at UC San Diego [79]. REDCap (Research Electronic Data Capture) is a secure, web-based application designed to support data capture for research studies, providing: 1) an intuitive interface for validated data entry; 2) audit trails for tracking data manipulation and export procedures; 3) automated export procedures for seamless data downloads to common statistical packages; and 4) procedures for importing data from external sources. Participants are assigned a study ID and all records are coded with the study ID rather than personal identifiers. All device data files will be kept on secure servers at the Social Sciences Computing Facility and data will only be accessible to investigators and project staff.

### Device measured outcomes

The primary outcomes are total PA and MVPA minutes per day, travel mode, and VMT. We will employ two best-available technologies, accelerometer and GPS devices, to objectively measure PA and location. These devices allow us to 1) precisely measure change in PA minutes and to specifically attribute any change in PA to LRT trips, and 2) determine travel mode to assess change in commute mode and VMT. 

### Minutes of MVPA

We will use Actigraph GT3X + accelerometers and process the data with Actilife software (ActiGraph, LLC; Pensacola, FL). Participants are asked to wear the device on a belt on their hip during waking hours for 7 days at each measurement point. Participants are asked to re-wear the devices if not worn for at least 10 h per day for 4 days to ensure data are representative of habitual PA [80–82]. We will use the established cut off of 1952 counts per minute (CPM) to determine minutes of MVPA during analysis [83]. To provide perspective on PA disparities reduction, we will assess the % of participants who meet PA guidelines of 150 min of MVPA per week.

### Travel mode share and VMT

GPS devices will be used to determine PA location, trip mode and trip distance. Participants will wear the Qstarz BT1000x GPS device (Qstarz International Co. Ltd., Taipei, Taiwan) to log X,Y location coordinates, distance, speed, elevation and time. The Qstarz GPS is smaller than a cell phone and is worn inside a pouch on the same belt as the accelerometer. Participants must charge this device every evening, and we have developed protocols to maximize adherence. The device captures data every 15 s and has an industry-reported accuracy of 3 m, with validation studies showing a median error of 2 m for bike and 3.9 m for walk trips [84]. We will use a validated imputation algorithm for missing data points [85]. After consideration of non-wear time and missing data, valid wear days of 10 h or more will be merged with the accelerometer data by time stamp at the minute level, using the HABITUS (Human Activity Behavior Identification Tool and data Unification System) [86]. HABITUS is a web-based service that processes these data to determine transportation trips, mode, routes, and distances travelled. VMT will be assessed using these data and self-reported vehicle odometer readings.

### Self-report measures and covariates

#### Equity Outcomes

Household expenditures and transportation costs will be assessed by self-report using survey measures from the Health and Retirement Study [87]. The Consumption and Activities Mail Survey captures information about healthcare, food, and transportation expenditures. The Health Care and Nutrition Survey considers whether health care access and nutrition spending were impacted by income (e.g., “In the last 12 months, did you ever eat less that you felt you should because there wasn’t enough money for food?”). All participants will be employed at baseline, but we will ask about changes in employment at all future assessments. Secondary human resource data will capture summary measures of new employees during the project period to determine the impact of the LRT line on employment opportunities (for example, a summary measure of the percentage of new employees using LRT as their primary commute method). Health care access and utilization will be assessed using questions from the Behavioral Risk Factor Surveillance System (BRFSS) survey.

Secondary health outcomes will be evaluated using validated self-report measures. We will use the 10-item Center for Epidemiological Studies-Depression Scale (CES-D Short-form), which is a commonly used population-based scale for measuring depressive symptoms in adults [88–90]. The 20-item Perceived Quality of Life scale (PQoL-20) asks participants to rate their satisfaction with various aspects of life [91], and the SF-12 Health Survey will measure health-related QoL [92, 93]. The Cohen Perceived Stress Scale measures the degree to which situations in one’s life are perceived as stressful [94]. To better understand sources of stress from discrimination and racism in our cohort, we included an additional measure of stress. The validated Everyday Discrimination Scale asks how often participants experience discrimination in their daily life based on their race, ethnicity or skin color [95–97]. The NIH PROMIS Sleep Disturbance 6a Short Form will assess perceptions of sleep quality, sleep depth, and restoration [98]. The Global Physical Activity Questionnaire allows us to capture self-reported PA in the occupational, transportation, and leisure domains [99, 100]. Participants will self-report height and weight, and BMI will be calculated (kg/m^2^) [101].

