### Equity aims

We will assess change in household expenditures, including transportation costs as a proportion of household income. We hypothesize the proportion of household income spent on transportation costs will decrease for those who utilize the new LRT, allowing for increased spending on health and QoL-related expenditures (i.e., healthy foods, medications, healthcare, etc.). We expect those with lower household income will have the largest decrease in transportation costs as a proportion of household income. We will additionally assess whether transit use is associated with an increase in the proportion of new UCSD hires from low-income areas and people of color, as well as potential impacts on employment continuity. 

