### Study sample and eligibility

Prior evaluations of new LRT have recruited people into treatment (exposed) and control groups based on distance from their homes to new rail stations [59–66]. There is debate on the degree to which LRT investments induce new transit ridership versus shifting existing users from bus to rail [57, 71–73]. The current study attempts to overcome this limitation by focusing recruitment on university staff who both live and work near the rail line. We are not recruiting students, given the longitudinal design, nor physicians/faculty, whose level of education and income would be higher than average and not generalizable to the broader population. Compared to faculty or students, UCSD staff live twice the average distance from campus, and roughly 50% live in areas accessed by transit [74]. To be eligible, participants must be 18 years of age or older, be a full or part-time employee at the UCSD La Jolla campus, have commuted to the La Jolla campus ≥ 2 days/wk prior to COVID-19 closures, have lived in the same location for at least 1 year with no plans to move, can walk without assistance, can read and write in English or Spanish, and spend most of their time in San Diego County. We aim to have equal distribution across distance to LRT groups (< 1 mile, 1–2 miles, > 2 miles), with 50% of the sample comprised by females, people of color, and low-income staff.

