We will perform additional sensitivity analyses to maximize covariate balance between LRT groups, considering techniques like inverse probability of treatment weighting (IPTW). IPTW removes confounding by creating a pseudo population in which every participant has an equal probability of being in the LRT- exposed group (i.e., home < 1 mile from LRT stop), assuming no unmeasured confounding. We will first model participants’ probability (i.e. the propensity score (PS) of being in the LRT-exposed group) [114] using imbalanced baseline demographic and environmental characteristics [115–117]. We will then calculate a weight using the PS values that will be included in regression models. Estimates from weighted and unweighted models will be compared and will also implement stabilized and truncated weights. We will examine the extent of missing data and conduct sensitivity analyses to compare characteristics of participants with complete versus incomplete data. Multiple imputation methods will be applied, assuming missing-at-random patterns and using default multiple imputation models (“mice” in R), with *N* imputed data sets generated (*N* corresponding the average % of missingness).

Test–retest reliability of the transit and COVID-19 survey measures, with two weeks in between assessments, will be assessed using intraclass correlation coefficients (ICC) [118, 119]*.* Values above 0.75 will be considered good to excellent reliability.

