## Discussion

The TROLLEY study has a unique opportunity to quantify change in key travel, health, and equity-related outcomes associated with the introduction of new LRT infrastructure and in the context of the COVID-19 pandemic. Research is needed to explore variables that may prevent increased vehicle dependence as a long-term consequence of the pandemic [53], and inform interventions to improve individual and climate health indicators. Despite promising cross-sectional evidence of associations between LRT and health, including MVPA, longitudinal evidence is less consistent [31, 36, 38, 120–122]. The TROLLEY study has the potential to document a more powerful effect than previous LRT evaluation studies based on the unique sampling of employees whose work location is newly accessed by LRT and who live near an LRT station. Low-income communities bear a greater burden from transportation costs and reliance on vehicles that negatively impacts health. Improving transit access may provide a cost-effective and long lasting approach to improve PA and health, with broad reach to lower income employees [123]. The TROLLEY study will improve our understanding of the mobility needs of vulnerable groups and transit as a workplace health and equity strategy.

The 2-year length of the study presents a challenge to participant retention. While we have planned for 20% attrition, the university sample allows more opportunity to maintain contact with participants and mitigate loss to follow up. The lack of accelerometer and GPS device data prior to the opening of the new LRT line limits our ability to detect true prospective associations between LRT and the outcomes under study. However, self-reported measures are likely to capture commute mode and frequency with sufficient accuracy to provide insight into change over time and the stratified sampling strategy and large sample size allow us to determine whether LRT, sociodemographic, and environmental factors modify change in outcomes. The state-of-the-science objective measures of PA, travel behavior, and built environments, in conjunction with 2-years of follow, strengthen our ability to capture a gradual uptake of LRT use and change in behaviors as the pandemic evolves.

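### Employment continuity is known only for participants who answer a later assessment, so the proportion leaving would be understated if leavers are harder to retain

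*Protocol article*

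**What the plan says.** The Equity aims section adds employment to the expenditure outcomes, "as well as potential impacts on employment continuity". Participants are UCSD staff by design: to enter, a person must "be a full or part-time employee at the UCSD La Jolla campus".

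For the cohort, the Equity Outcomes section gives one way of learning about job changes: "All participants will be employed at baseline, but we will ask about changes in employment at all future assessments". Data collection states that "Participants will be assessed 3 times during the 2 years they are enrolled in the study" (enrolment, one year and two years), so a change can be reported on two occasions.

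The same section brings in employer records for another purpose: "Secondary human resource data will capture summary measures of new employees during the project period". These are aggregates about people joining, not individual records of enrolled participants leaving.

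On retention, the Discussion assumes 20% attrition and argues that "the university sample allows more opportunity to maintain contact with participants and mitigate loss to follow up". It also says that devices are handed out at campus locations. On missing data, the Statistical approach says "Multiple imputation methods will be applied, assuming missing-at-random patterns", alongside a comparison of participants with complete and incomplete data.

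**The concern.** A job change enters the data only if the person completes a later assessment. The article's reason for expecting good retention is the link with the university, and leaving the university weakens that link. Whether the outcome is observed may therefore depend on the outcome.

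The planned safeguards do not address this. Imputation under missing at random gives non-responders the leaving rate of responders with similar recorded data. Comparing complete with incomplete participants on baseline data cannot show who later left, because everyone is employed at baseline. The HR summaries describe joiners.

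At stake is the absolute level of job retention in the cohort, and any absolute difference in it by distance, income or transit use. The primary outcomes are not affected by this point.

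**Working it through.** The article gives no rate, sample size or power for employment continuity, so there is no figure to reproduce. The check shows the direction of the bias and how its size depends on unknowns.

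**Inputs from the article.** N = 465 (Sample size: "The TROLLEY study will enroll 465 English or Spanish speaking staff from UCSD’s La Jolla campus"); overall loss 20% (Sample size and Discussion).

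**Assumptions.** p = true proportion leaving over two years; k = loss among leavers divided by loss among stayers. The article gives neither.

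**Formulas**
- Loss in stayers = 0.20 / (1 − p + p·k)
- Loss in leavers = k × loss in stayers
- Observed proportion leaving = p × (1 − loss in leavers) / 0.80
- True proportion leaving among non-responders = p × loss in leavers / 0.20

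**Results for p = 10%** (0.10 × 465 = 46.5 leavers)

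| k | Loss, stayers | Loss, leavers | Leavers seen | Observed proportion | True proportion among non-responders |
|---|---|---|---|---|---|
| 1 | 20.0% | 20.0% | 37.2 | 10.0% | 10.0% |
| 1.5 | 19.0% | 28.6% | 33.2 | 8.9% | 14.3% |
| 2 | 18.2% | 36.4% | 29.6 | 8.0% | 18.2% |
| 3 | 16.7% | 50.0% | 23.25 | 6.2% | 25.0% |
| 4 | 15.4% | 61.5% | 17.9 | 4.8% | 30.8% |

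For k = 3: 0.20 / (0.90 + 0.30) = 0.1667; 3 × 0.1667 = 0.50; 0.10 × 0.50 / 0.80 = 0.0625.

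Over p from 5% to 30%, the relative understatement is 14% to 23% at k = 2 and 22% to 43% at k = 3. At k = 1 the proportion is unbiased and only the count is short, by 20%.

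**Effect of imputation.** Suppose recorded data do not predict who left. Imputation then gives non-responders the responders' rate. At k = 3 the total stays at 0.80 × 6.25% + 0.20 × 6.25% = 6.25%, whereas the truth is 0.80 × 6.25% + 0.20 × 25% = 10%. Covariates that predict leaving would recover part of the gap, but not the part in which response depends on leaving itself.

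**Effect on a comparison by exposure.** Assume true leaving of 15% near the line and 25% far from it, with 50% of leavers and 87.5% of stayers responding in both groups. At the average leaving rate of 20%, response is 0.20 × 0.50 + 0.80 × 0.875 = 80%, as planned.
- Near, observed: 0.075 / (0.075 + 0.74375) = 9.2%
- Far, observed: 0.125 / (0.125 + 0.65625) = 16.0%
- Risk difference: 10 points true, 6.8 observed
- Risk ratio: 0.15 / 0.25 = 0.60 true, 0.573 observed
- Odds ratio: (0.15/0.85) / (0.25/0.75) = 0.529 true; (0.075/0.74375) / (0.125/0.65625) = 0.529 observed

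The odds ratio is unchanged because the ratio of leavers' to stayers' response multiplies the odds in both groups and cancels. If that ratio differs between groups, the odds ratio is multiplied by the quotient of the two ratios and can move in either direction.

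**The case against.** The strongest objection concerns the effect scale. A reader might infer that any link between transit access and job retention is pulled toward zero, or that this part of the equity aim cannot be answered from responders. The documents do not support that. The Statistical approach plans logistic models for categorical outcomes. If response depends on leaving in the same way in every exposure group, the odds ratio is unbiased, and in the example the risk ratio moves slightly away from the null. Only the absolute scale shrinks. The article does mention an additive scale, when it discusses effect modification. This objection stands and limits the point.

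Leavers are also not out of reach. Contact details and a home address or nearest intersection are taken at screening, survey links are emailed, staff telephone participants during the wear week, and each completed time point is paid. Nothing in the article withdraws leavers. This stands too: some will respond, and higher loss among them is an expectation, not a documented fact.

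The article condenses a fuller protocol that may describe tracing. That is fair for procedures. But the article does state the source for cohort job changes and the scope of the HR data, and an analysis plan cannot recover departures that nobody recorded.

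Finally, the article never equates continuity with staying at UCSD. Someone who moves straight to another employer may count as continuously employed, and UCSD records could not show that. This is a good reason not to replace self-report with HR records.

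**Conclusion.** The point holds for absolute quantities. Employment continuity in the cohort rests on participant report alone. If leavers respond less than stayers, the leaving proportion is too low, and so are absolute differences of the kind shown above. Missing-at-random imputation does not repair this.

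The size is unknown. At 20% loss and an assumed 10% leaving, the observed figure runs from 10.0% (equal loss) through 8.0% (twice the loss) to 6.2% (three times). All leaving and response rates here are assumptions. Bias in an odds ratio needs a further condition, that the dependence of response on leaving differs by exposure, and the documents give no evidence for or against it.

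This is worth correcting because it is cheap and cannot be recovered later. It concerns one component of the equity aims and leaves the primary outcomes untouched.

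**What to change.** - **Data collection.** At 12 and 24 months, send every participant who does not attend a single employment-status question by personal email or telephone: still at UCSD, employed elsewhere, or not employed, with the date of any change. Ask for a personal email address and telephone number where only work details are held.
- **Analysis.** Include these answers in the continuity analysis. State whether continuity means remaining at UCSD or remaining in any employment; the three answer categories serve both.
- **Sensitivity analysis.** Let the remaining non-responders have higher leaving rates than responders over a stated range, and report the overall proportion and the exposure contrasts across it. The last two columns of the table show the sort of gap to cover, for example 18.2% against 8.0%, or 25.0% against 6.2%.
- **Optional supplement.** For participants who consent, add active or separated status with date from HR records. This covers UCSD employment only and should not replace the self-reported answer.

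The cost is a small contact effort at two time points. HR status would also need a consent addendum and ethics approval. The article reports 230 already enrolled, who would have to be asked again; the other 235 of 465 could be asked at entry. Some staff may not want their employer's records linked, which is why this part should stay optional.
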